**Figure 1 F1:**
[figure not shown]
Participants’ process throughout the trial. NHS, National Health Service; OT, occupational therapy; OTTER II Trial, Osteoarthritis Thumb Therapy II Trial.

### Qualitative interviews

Between weeks 8 and 12, a qualitative telephone interview will take place for a subgroup of patients in intervention arms B and C. The researcher will be blinded for the qualitative interviews to prevent bias related to treatment allocation during data collection. In order to make this practical, the researcher carrying out data collection will be independent from the RCT and will be unfamiliar with the splints and differences between them. The methodological approach for the qualitative study will be a framework analysis. Purposive sampling will be used and based on male to female ratio (as per the study sample); age and AUSCAN hand pain index at baseline. Interviews will be conducted with up to 40 participants. Interviews will be semistructured, using a topic guide informed by patient partners, to elicit experience of splint and self-management interventions, splint preference, adherence and views about reasons for effectiveness. There will be a password for each participant that has agreed to take part in the interview study so that the participant can be correctly identified on the telephone. Consent for participation in the qualitative interview will be sought and given at the time of entry into the main study.

The schedule of enrolment, interventions and a summary of assessments are shown in table 2. Detailed information about baseline assessments and outcome measures are listed in table 3.

**Table 2 T2:** Schedule of enrolment, interventions and assessments

Time point:	Study period							
	Enrolment	Allocation	Post-allocation					Close-out
	Baseline day 0	Baseline day 0	2 weeks	4 weeks	8 weeks	9–11 weeks	12 weeks	After 12 weeks
Enrolment:								
Eligibility screen*****	X							
Informed consent*	X							
Randomisation/allocation		X						
Interventions:								
Optimal NHS self-management care		X 						
Optimal NHS self-management care plus verum splint		X 						
Optimal NHS self-management care plus placebo splint		X 						
Telephone call check of progress			X					
Review of self-management care and splint wear (if applicable)				X				
Assessments:								
Baseline assessments: see table 3	X							
Outcomes: Grip Ability Test^40^				X	X			
Outcomes: see table 3					X			
Outcomes at follow-up: See table 3							X	
Exercise adherence								
Splint adherence								
Qualitative interviews (selected participants)						X		
Patient request for further treatment								X

*The eligibility screen and informed consent can optionally be carried out prior to time point 0.

NHS, National Health Service.

**Table 3 T3:** Baseline assessment and outcome measures

Measure	Screening	Baseline	4 weeks	8 weeks	12 weeks
Work Productivity and Activity Impairment Questionnaire)^48^		✓		✓	✓
Generic Quality of Life (SF12-V2)^53^		✓		✓	✓
EuroQol 5 Dimensions 5-Levels questionnaire^46^		✓		✓	✓
AUSCAN hand stiffness^42^		✓		✓	✓
Michigan Hand Questionnaire^54^		✓		✓	✓
Thumb pain over the last week		✓		✓	✓
Disability of the arm, shoulder, hand questionnaire^55^ Leisure section only		✓		✓	✓
Arthritis Self-Efficacy Pain Scale^56^		✓		✓	✓
AUSCAN hand pain^42^	✓			✓	✓
AUSCAN hand function^42^	✓			✓	✓
Global assessment of change^41^				✓	✓
Health utilisation questionnaire				✓	✓
The objective clinician assessed Grip Ability Test^40^		✓	✓	✓	

The Global Assessment of Change^41^ question adapted for the OTTER II study asks ‘With respect to your thumb base pain how would you describe yourself now as compared with the start of your OTTER Trial therapy treatment’. The answer is given on a five-point Likert scale, that ranges from ‘very much worse’, ‘worse’, over ‘no change’ to ‘better’ and ‘completely recovered’. The AUSCAN hand index for pain^42^ recorded at baseline and 8 weeks is the primary outcome measure. The CRFs for this study can be obtained from the first author [name]

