### Trial design and setting

The Osteoarthritis Thumb Therapy (OTTER) II Trial is a pragmatic, multi-centred, single (participant) blind, superiority randomised controlled clinical effectiveness and efficacy trial. People with symptomatic thumb base OA reporting moderate to severe thumb base pain, will be equally allocated to one of three groups: Group A: 8 weeks of a facilitated self-management programme, Group B: 8 weeks of a facilitated self-management programme plus a verum splint or Group C: 8 weeks of a facilitated self-management programme plus a placebo splint. All groups will be encouraged to continue their self-management and, where appropriate, splint wear until follow-up at 12 weeks from baseline. The study will run from 28th February 2017 to 14th March 2019.

Participants will be recruited consecutively from referrals to occupational therapy or physiotherapy (Therapy) departments from new, current and review patients of Rheumatology, Orthopaedic, Hand Surgery Units and General Practice at 17 NHS recruitment sites (online supplementary appendix 1). Intervention will be delivered by a qualified OTTER II Trial trained occupational therapist or physiotherapist who has worked independently in a clinical role treating patients with hand OA and who works within a therapy department that accepts referrals for patients with thumb base OA.

10.1136/bmjopen-2018-028342.supp2Supplementary data

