Participants will be blind to treatment allocation. Strategies to maximise participant blinding include training for trial clinicians in how to present and discuss the treatment arms positively without disclosing other treatment options and routine assessment included in the quality assurance trial monitoring visits of clinician’s communication and interaction in presenting treatment options with participants. The PIS has been carefully worded to state that an element of the self-management intervention may be placebo but does not state what aspect this may be. The study will be described as a comparison of self-management interventions and not divulging detail about placebo splinting in any clinician communication. Trial participants will not receive group intervention and therefore cannot compare their interventions received and we will not include participants who have already received thumb base splints. All of these strategies will help to maintain participant blinding. Contamination between treatment arms will be limited by identifying on hospital notes that the patient is part of the OTTER II Trial and therefore should not receive any further hand therapy treatment from the hospital team. It is not possible to prevent participants allocated to arm A or C purchasing their own splints during the trial period; however, the data will be captured in the final study questionnaire and will be used to assess any degree of contamination. The OTTER II Trial placebo splints will not be able to purchased privately.

This approach will support participant blinding, in addition to the training that treating therapists will receive about delivering placebos and responding to participant questions. The success of participant blinding will be assessed via patient questionnaires at 12 weeks.

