### Treatment and follow-up

Figure 1 flowchart shows the participants’ progress through the trial. After randomisation, participants will receive their allocated intervention during a 60 min appointment (week 0). All participants in each treatment arm will receive a 10 min telephone call at 2 weeks from the therapist to check for adherence to the self-management programme and to discuss any problems identified by the participant as relevant. In addition for Groups B and C participants, the therapist will check splint wear and comfort. Participants will attend for a 30 min appointment 4 weeks after randomisation, to review treatments and make adjustments where necessary and an assessor blind to treatment allocation will administer the objective Grip Ability Test^40^. A final hospital visit occurs 8 weeks after randomisation. A paper questionnaire will be posted to each participant at 12 weeks to collect follow-up patient-reported outcomes. After the 12-week follow-up has been completed (study endpoint), all patients will be offered the option of a further follow-up appointment for any further care that is needed. If patients have received verum splints, then they may keep these, if patients have received placebo splints or self-management alone then they will be offered the opportunity to receive a verum splint if required.

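### Up to 40 participants from the two splint arms are interviewed about their splint in weeks 9 to 11, ahead of their 12-week self-reported outcomes and blinding questionnaire; arm A has no counterpart (minor, easily avoided)

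*Protocol article*

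**What the plan says.** The Qualitative interviews section of the protocol article states: "Between weeks 8 and 12, a qualitative telephone interview will take place for a subgroup of patients in intervention arms B and C". It limits the number: "Interviews will be conducted with up to 40 participants". The topics include "splint preference, adherence and views about reasons for effectiveness". In Table 2 the only mark in the interview row is in the 9–11 weeks column, immediately before the 12-week outcome column. No interview is described for arm A.

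Treatment is still running at that time. Trial design and setting says: "All groups will be encouraged to continue their self-management and, where appropriate, splint wear until follow-up at 12 weeks from baseline". Treatment and follow-up then says: "A paper questionnaire will be posted to each participant at 12 weeks to collect follow-up patient-reported outcomes". Table 3 lists what is repeated at 12 weeks, including AUSCAN pain, function and stiffness, thumb pain, self-efficacy, global change and EQ-5D-5L. The blinding check falls at the same point (Randomisation section): "The success of participant blinding will be assessed via patient questionnaires at 12 weeks". The primary outcome is earlier: the text under Table 3 says AUSCAN pain "recorded at baseline and 8 weeks is the primary outcome measure".

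**The concern.** Elsewhere the plan keeps scheduled contact even across arms. All three arms receive 90 minutes of direct therapy, the same visits and a 10-minute call at 2 weeks, and arm A spends more of its time on self-management. The interview is the one scheduled contact that an arm A participant cannot receive.

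Talking at length about a splint, how it is used and why it might work could change how a person uses it in the remaining weeks, or how they rate pain and change at week 12. Any such reaction would fall only in arms B and C, so B versus A and C versus A at 12 weeks could not separate it from an effect of being given a splint. The 12-week cost-utility analysis uses the same EQ-5D responses.

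The blinding check is exposed too. Participants are told only that some part of the self-management intervention may be placebo, not which part. A call centred on the splint may draw attention to it shortly before they are asked about blinding. This matters more here than in many trials, because the Introduction gives non-specific and contextual effects as part of the reason for doing the study.

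**Working it through.** **The plan's own figure first.** Inputs from Sample size: 80% power, 5% two-sided, a 2-point difference, SD 5, 20% loss at 8 weeks. A global F test for three arms with means 0, 0 and 2 and SD 5 gives 92 per arm (power 0.803). Then 92 / 0.80 = 115 per arm and 3 × 115 = 345. The sample size reproduces and is not in dispute; it supplies the denominators below.

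**Share of participants exposed.**
- Randomised to B and C: 2 × 115 = 230. Share = 40 / 230 = 17.4%.
- Retained in B and C: 2 × 92 = 184. Share = 40 / 184 = 21.7%. This uses the 8-week loss; the section gives no 12-week figure.
- Arm A: 0%.

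Both shares are maxima, because 40 is an upper limit in the Qualitative interviews section.

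**What a reaction could do to the arm means.** The document gives no effect of an interview. Purely as an assumption, let each interviewed person's 12-week AUSCAN pain shift by *e* points, all in the same direction. The shift in the pooled B and C mean is *e* × share.

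| *e* (assumed) | × 40/230 | × 40/184 |
|---|---|---|
| 0.5 | 0.09 | 0.11 |
| 1 | 0.17 | 0.22 |
| 2 | 0.35 | 0.43 |

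Against SD 5 the range is 0.09 / 5 = 0.02 to 0.43 / 5 = 0.09 standardised units. Against the 2-point target it is 4% (0.087 / 2) to 22% (0.435 / 2). The upper end requires one telephone call to move pain by the whole difference the trial is powered to detect, so it is a bound and not an expectation.

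**Balance between B and C.** If the 40 are split evenly and react alike, the shift cancels in B versus C. The purposive sampling criteria are sex ratio, age and baseline AUSCAN pain; arm is not among them, so an even split is not guaranteed. In the extreme case of all 40 from one arm, the share is 40 / 115 = 34.8% or 40 / 92 = 43.5%. The shift in that arm is then 0.17 (0.5 × 0.348) to 0.87 (2 × 0.435) points under the same assumption.

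**Outcomes that can be affected.** The interviews follow the 8-week visit in Table 2, so the primary outcome, the other 8-week outcomes and the 8-week cost-utility analysis come before them. The Grip Ability Test is not repeated at 12 weeks. What remains is the 12-week self-report, the 12-week economic analysis and the blinding questionnaire.

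**The case against.** The strongest reply is that this is a deliberate, scheduled research call, consented at entry. It is made by a researcher who is independent of the trial, blind to allocation and unfamiliar with the splints. It elicits experience; no advice or coaching is described. Interviewing soon after week 8 also keeps recall fresh, and nothing in the document contradicts that timing. All of this stands, and it makes a large effect unlikely. It does not remove the asymmetry: blinding the interviewer protects the interview data, but it does not stop a participant reacting to the conversation.

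Three stronger readings are tempting and are not supported.
- A reader might infer that the 12-week outcomes of the splint arms as a whole follow an extra contact. At least 78% of those retained in B and C (83% of those randomised) never have one.
- A reader might call the interview an unplanned co-intervention. It is planned; what may be unintended is any effect on outcomes.
- A reader might take 22% of the target difference as the size of the bias. That figure combines the largest assumed reaction, the maximum number of interviews, a single direction of shift and the smaller denominator. The document contains no evidence of reactivity at all.

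It is also fair that a sensitivity analysis could be left to the statistical analysis plan, which is not shown. The point here is the schedule, which this document does fix.

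**Conclusion.** The point holds at low severity. The schedule creates an avoidable difference in contact between arm A and the splint arms before the 12-week self-report and the blinding check. It reaches at most 17% of those randomised to B and C, or 22% of those retained if the 20% loss assumed at 8 weeks also applies at 12 weeks.

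Its effect on B versus A and C versus A at 12 weeks is of unknown size and probably small; the shifts tabulated above rest wholly on an assumed reaction. Sparing B versus C depends on interviews being balanced between those arms and on similar reactions in each. The primary conclusion at 8 weeks and the sample size do not change.

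**What to change.** In the Qualitative interviews section and Table 2, schedule each interview for when that participant's 12-week questionnaire has been received, or when the postal and telephone chasing described under Data collection, management and analysis has ended. The exposed share is then 0% in every arm for every questionnaire returned. State that the interview must not delay the post-trial offer of further care described under Treatment and follow-up.

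If interviews have already been held, report the 12-week outcomes with and without interviewed participants as a sensitivity analysis. This is the weaker remedy, because it removes people chosen after randomisation from two arms with no matching removal in arm A.

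The cost is small: the interviewer, the number of interviews and the sample size stay the same. Recall of the 8-week treatment period is a few weeks older, and some coordination is needed so that the interview fits around the chasing of questionnaires and the offer of care.

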### Sample size

The sample size has been calculated based on undertaking a global analysis of covariance (ANCOVA) for the primary outcome, AUSCAN hand pain^42^ at 8 weeks, adjusting for the baseline pain score and stratification factors (including centre and treated hand dominance) across all three treatment arms using the power and sample size package, PASS 11 (PASS 11. NCSS, LLC. Kaysville, Utah, USA. www.ncss.com). Assuming 80% power, a 5% two-sided significance in order to detect a standardised mean difference of 0.4 (a moderate effect size^43^ based on a difference in the AUSCAN hand pain score of 2 points) and assuming a SD of 5, based on data from the OTTER pilot study,^31^ requires 92 participants per arm. Allowing a 20% loss to follow-up at 8 weeks inflates this to 115 participants per arm, giving a total of 345 participants.

The sample size has taken into account the global comparison of the null hypothesis that there is no difference between the three treatment arms, and pairwise comparisons will only be undertaken if this global comparison is statistically significant. No further adjustment for the sample size has been undertaken to allow for multiple testing.

Clustering is not a consideration in sample size as ‘Centre’ is a stratification factor, and although there may be more than one therapist per centre, this should largely ensure balance across treatment arms within each centre. The Data and Safety Monitoring Committee (DSMC) (online supplementary appendix 8) will review the assumptions underlying this sample size calculation after approximately 50% of the participants have been recruited and followed up for 8 weeks, if still within the recruiting period.

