An independent DSMC (online supplementary appendix 8) will be convened with two expert clinicians and a statistician to regularly review accumulating data in order to assess patient safety and study conduct following the recommendations of the DAMOCLES study^51^ with full details being provided in a charter. They will advise the Trial Steering Committee (online supplementary appendix 9) as to whether recruitment should stop early, which is only likely to occur if either intervention is shown to be unsafe for patients. As this is a low-risk study, no interim efficacy comparative analyses are planned and no safety issues are expected. The OTTER II Trial team will have access to the final trial dataset and there will be no public access to patient level data or the statistical code used within the trial.

We believe this to be the first fully powered placebo controlled splinting trial exploring the effectiveness and efficacy of splints in symptomatic thumb base OA. Study results will be disseminated to rheumatology, hand therapy, occupational therapy and physiotherapy national and international conferences and submitted for consideration in international and national academic and professional conferences and journals. Lay publications written in accessible language will be provided to charitable, community and patient facing publications as recommended by our patient and public involvement partners. Study participants will be provided regular updates of the study progress through the OTTER II study website.

10.1136/bmjopen-2018-028342.supp1Supplementary data

10.1136/bmjopen-2018-028342.supp3Supplementary data

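### The 80% power belongs to the global three-arm test under one unstated pattern of means; it does not carry over to the pairwise splint questions for which the article says the trial is powered

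*Protocol article*

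**What the plan says.** The Sample size section of the protocol article bases the calculation on the global test of AUSCAN pain at week 8: "The sample size has been calculated based on undertaking a global analysis of covariance (ANCOVA) for the primary outcome". The inputs begin with "Assuming 80% power, a 5% two-sided significance in order to detect a standardised mean difference of 0.4". The article describes that effect as "based on a difference in the AUSCAN hand pain score of 2 points". For the spread it gives "assuming a SD of 5, based on data from the OTTER pilot study". The stated result is "requires 92 participants per arm". Attrition is then handled as follows: "Allowing a 20% loss to follow-up at 8 weeks inflates this to 115 participants per arm, giving a total of 345 participants". The section adds that pairwise comparisons follow only a significant global result, and that "No further adjustment for the sample size has been undertaken to allow for multiple testing".

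The Statistical analysis section makes the absence of any difference among the three arms the primary null hypothesis. It lists three pairwise comparisons after rejection and expects a multiplicity adjustment at that stage, by Bonferroni or something less conservative.

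The trial questions at the end of the Introduction are whether adding a splint to self-management helps, and whether verum and placebo splints differ. The strengths and limitations box states that the trial is powered for the first of these. The Ethics and dissemination section calls it "the first fully powered placebo controlled splinting trial".

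The article gives neither the pattern of the three means nor the power of any pairwise comparison.

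**The concern.** The power of a three-group F-test depends on where all three means lie, not only on the largest difference. For a fixed largest difference, power is highest when two arms coincide and lowest when the third is midway. The Introduction motivates the placebo arm by a possibly substantial non-specific effect of splinting, so an intermediate placebo mean is a realistic case.

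Both trial questions are answered by pairwise comparisons, which must pass the global test and then, in all likelihood, an adjusted threshold. Neither step is reflected in 92 per arm. A reader of the strengths box could therefore take a non-significant verum versus self-management result as coming from a comparison with 80% power, and read it as firmer evidence against splints than it is.

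**Working it through.** **Inputs** (Sample size section): difference 2, SD 5, two-sided 5%, 92 evaluable per arm, 20% loss. Allocation is 1:1:1 (Randomisation section). Arms: A self-management, B verum, C placebo. Means are written as benefit relative to A.

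**Step 1: reproduce 92.** For the global test, λ = n·Σ(μᵢ − μ̄)²/SD², referred to a noncentral F with 2 and 3n − 3 degrees of freedom.

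- One arm apart, (A, B, C) = (0, 2, 0): μ̄ = 2/3 and Σ = 4/9 + 16/9 + 4/9 = 24/9 = 2.667. λ = 92 × 2.667/25 = 9.81. With critical F(2, 273) = 3.03, power is 80.3%. At 91 per arm it is 79.8%, so 92 is the smallest n that reaches 80%. The pattern (0, 2, 2) gives the same value.
- 92/0.8 = 115 per arm, and 3 × 115 = 345.
- A two-arm t-test at 5% would need 100 per arm, so 92 is not a pairwise sample size.

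No covariate gain enters this reproduction. SD 5 acts as the residual SD.

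**Step 2: placebo midway, (0, 2, 1).** Σ = 1 + 1 + 0 = 2 and λ = 92 × 2/25 = 7.36. Global power is 67.4%; 122 per arm would be needed for 80%.

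**Step 3: pairwise power for a true 2-point difference.** The noncentrality is (2/5)·√(92/2) = 2.713. On 273 degrees of freedom, the critical t is 1.969 at 0.05 and 2.409 at 0.05/3 = 0.0167. Power is 77% unadjusted and 62% with Bonferroni, before the global test is required.

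**Step 4: global test first, then pairwise tests** (simulation, 400,000 replicates, 92 per arm, residual SD 5):

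| Comparison and pattern | Bonferroni | Holm | No further adjustment |
|---|---|---|---|
| B vs A, C equal to A | 62% | 65% | 72% |
| B vs C, C equal to A | 62% | 65% | 72% |
| B vs A, C midway | 61% | 62% | 66% |
| B vs C, C midway (1 point) | 15% | 19% | 26% |

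When B and C are equal and both 2 points from A, B vs A again has 62%, 65% and 72%. With two arms equal, Tukey gives 63% and Hochberg 66%.

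**Step 5: if 5 is the raw SD.** The residual SD is then 5·√(1 − R²). The article gives no R², so these values are assumptions.

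| Assumed R² | Residual SD | Global, two equal / midway | B vs A, Bonferroni | B vs A, Holm |
|---|---|---|---|---|
| 0 | 5.00 | 80% / 67% | 61–62% | 62–65% |
| 0.25 | 4.33 | 91% / 80% | 76% | 77–79% |
| 0.30 | 4.18 | 93% / 83% | 79–80% | 80–83% |
| 0.36 | 4.00 | 95% / 86–87% | 83–84% | 84–86% |

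Ranges in the last two columns run from placebo midway to two arms equal.

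**The case against.** The strongest reply is that the article sizes on its declared primary hypothesis and says so: the calculation is global, pairwise tests are conditional, and nothing was added for multiplicity. Sizing on a global test is a legitimate choice, and a condensed article may leave the mean pattern to the full protocol. This stands as far as the Sample size section goes. It does not cover the strengths box, which moves the power claim to a pairwise question.

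A second reply is that ANCOVA on baseline pain adds precision. That is right if 5 is the raw SD: the verum versus self-management shortfall under Bonferroni all but closes near R² = 0.30. But 92 reproduces with no such gain, and the article neither says which SD is meant nor states an R².

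Three stronger readings are tempting, and the document does not support them.

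- That the sample-size arithmetic is wrong. It is not; 92, 115 and 345 all reproduce.
- That power is 62% for both trial questions under the plan. Bonferroni is only one permitted method, and the verum versus placebo figure depends on where placebo lies: it is 62% to 72% if placebo equals self-management, and much lower if placebo is midway.
- That the trial must be enlarged. Type I error and the estimates are unaffected, and the data and safety monitoring committee is already due to review the sample-size assumptions at about half recruitment.

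The claim in the Ethics and dissemination section is general wording, set against the small, non-powered studies mentioned in the Introduction. Alone it would hardly merit comment.

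**Conclusion.** The point holds as an error in the scope of the power claim, and it should be fixed. On the stated inputs, with 5 as residual SD, 80% applies to the global test when one arm lies 2 points from two equal arms; it falls to 67% with placebo midway. A true 2-point verum versus self-management difference is declared significant with about 61% to 72% power, depending on the multiplicity method and the placebo mean. Verum versus placebo matches the 62% to 72% only if placebo has no effect beyond self-management; with placebo midway, where the true difference is 1 point, it has about 15% to 26%.

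That 92 per arm does not show 80% pairwise power on these inputs is certain. The size of the shortfall is conditional: it narrows to a few points at an assumed R² of 0.25 and may vanish for verum versus self-management from about 0.30.

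**What to change.** Keep 345 participants and the planned analysis. In the Sample size section:

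1. State the pattern of means behind 92 per arm, and that 80% refers to the global test under that pattern. Give the midway-placebo value beside it (67% on the present inputs).
2. State whether SD 5 is raw or residual, with any R² assumed for baseline adjustment.
3. Give the power for verum versus self-management and for verum versus placebo, after the global test and under the multiplicity method chosen, with placebo equal to self-management and with placebo midway.

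Then reword the strengths box, and the general claim in Ethics and dissemination, so that they describe power for the global comparison.

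The cost is a few sentences and a less favourable power statement. No extra patients are needed, and the monitoring committee's planned review would have explicit assumptions to check.
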